### Design

A two-arm cluster randomized controlled trial (RCT) will be conducted. Participants’ school classes will be randomized by a computer software (www.randomizer.org) in one of the two treatment conditions: (1) video-based transdiagnostic REBT universal prevention program or (2) waitlist control. Assessments will be conducted at four time points: baseline (T_1_), post-intervention (T_2_), 3 months follow-up (T_3_) and 12 months follow-up (T_4_). Figure 1 illustrates the flowchart of the study.

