### Sample size calculation

A priori power analyses using G*Power version 3.1.5 [42] indicated that a total sample size of 260 would be sufficient to detect a small to medium effect size (*d =* .35) according to the results or previous research, for a two-tails between-group comparison at posttest, with an alpha of .05 and a power of 80%. As we expected to have a 30% dropout rate, we will recruit 169 participants in each group.

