### Statistical methods

Statistical analyses were conducted using SPSS 23.0 software. First, independent t-tests and Chi-Square tests will be conducted in order to explore potential differences between participants from the two groups regarding age, gender, anxiety, depressive symptoms, irrationality, comorbid conditions, and quality of life. At post-treatment (T2), three months follow-up (T3) and twelve months follow-up (T4), continuous analysis will be conducted using intent-to-treat (ITT) principle the last observation carried forward. In order to assess the efficacy of the video-based transdiagnostic REBT universal prevention program to reduce anxiety and depressive outcomes as compared with the control group over time, we will use mixed effects models (random intercept and slope for time, a fixed effect for group). For effect size data we will use Cohen’s *d* (small effect size *d* = .20, medium effect size *d* = .50, large effect size *d* = .80; [52]). Mediation and moderation analyses will be conducted using PROCESS macro [53].

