Key inclusion and exclusion criteria	Inclusion criteria: Preadolescents and adolescents will have ages between 12 and 17 years old; Are attending middle school or high-school; Adolescents have sufficient understanding of the Romanian language in order to complete assessments at all time points and to participate in the prevention program; Their parents have sufficient understanding of the Romanian language in order to sign the informed consent; Parents will sign the informed consent and adolescents will provide informed assent. Exclusion criteria: Age below 12 or above 17 years; No signed informed consent from parents; Adolescents will score high on suicidal ideation according to (1 item on the Depression subscale from Beck Youth Inventories); Not Romanian-speaking in order to understand the content of the prevention program and to complete the assessments.
Study type	Randomized controlled trial
Date of first enrollment	June 2016
Target sample size	338
Recruitment status	Recruiting
Primary outcome(s)	Anxiety symptoms at T_2_, T_3_, T_4_; the Multidimensional Anxiety Scale for Children Depressive symptoms at T_2_, T_3_, T_4_; the Beck Youth Inventories™ -Second Edition for Children and Adolescents
Key secondary outcome(s)	Maladaptive cognitions at T_2_, T_3_, T_4_; the Children’s Automatic Thoughts Scale – Negative/Positive Comorbid problems at T_2_, T_3_, T_4_; the Strengths and Difficulties Questionnaire Prosocial behaviors Quality of life at T_2_, T_3_, T_4_; the Questionnaire for Measuring Health-Related Quality of Life in Children and Adolescents, The Revised Version – adolescent version Treatment expectancies at T_2_; the Credibility/ Expectancy Questionnaire Satisfaction with the intervention at T_2_; the Client Satisfaction Scale

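### The efficacy model has one constant group effect and no group-by-time term, so it estimates neither the T2, T3 and T4 effects nor the posttest contrast that was powered

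*Protocol article*

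**What the plan says.** All references are to the protocol article.

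- **Statistical methods**, purpose of the model: "to reduce anxiety and depressive outcomes as compared with the control group over time, we will use mixed effects models". Its terms follow at once: "random intercept and slope for time, a fixed effect for group". Neither this section nor any other names a group-by-time term or a baseline covariate. The T1 scores appear only in preliminary checks: "independent t-tests and Chi-Square tests will be conducted in order to explore potential differences between participants from the two groups".
- **Statistical methods**, preceding sentence, which lists T2, T3 and T4: "twelve months follow-up (T4), continuous analysis will be conducted using intent-to-treat (ITT) principle the last observation carried forward".
- **Design**: "Assessments will be conducted at four time points: baseline", followed by post-intervention, 3 months and 12 months. School classes are the units randomised.
- **Table 2, primary outcomes** (under Ethics and dissemination): "Anxiety symptoms at T_2_, T_3_, T_4_; the Multidimensional Anxiety Scale for Children", with depressive symptoms at the same three times.
- **Sample size calculation**: 260 participants for d = 0.35, "for a two-tails between-group comparison at posttest, with an alpha of .05 and a power of 80" per cent.

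**The concern.** The question is whether anxiety and depression develop differently in the two arms, and by how much at each of three visits. In a longitudinal model the group-by-time term answers that. The random slope does not replace it: it lets individuals differ in their trend, but the mean trend stays the same in both arms. What is left is one group coefficient, which is a weighted average of the between-arm differences at the occasions used as responses.

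Three things are at stake:

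- The trial would report a number that is not the effect at T2, T3 or T4, so the follow-up visits could not show whether the benefit fades, lasts or grows.
- The contrast behind the sample size would not be the one tested.
- If T1 is a response, an occasion with an expected difference of zero enters the average. That pulls the estimate towards zero and lets a chance imbalance at T1 contribute directly.

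**Working it through.** **1. The plan's own figure.** With a two-sided alpha of 0.05, 80% power and d = 0.35, the normal approximation gives n per arm = 2 × (1.960 + 0.842)² / 0.35² = 128.1, so 129. The exact noncentral t gives 130 per arm, 260 in total, with power 80.3%. The stated 260 is reproduced, and it belongs to a difference at T2.

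**2. What the group coefficient estimates.** With equal arms and complete data, let D be the vector of between-arm differences at the response times and V the within-person covariance matrix. The generalised least squares coefficient is w′D, with w = V⁻¹1 / (1′V⁻¹1). It does not depend on how the fixed effect of time is coded, or on whether there is one, because both arms share it.

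**3. Assumptions (not in the documents).** SD is 1 at T1, intercept variance 0.6, residual variance r = 0.4, slope variance s from 0 to 0.05, intercept and slope uncorrelated, time coded t = 0, 1, 2, 3. Clustering and missing data are ignored. Then w at time t is proportional to 1 − t × sΣt / (r + sΣt²), with Σt = 6 and Σt² = 14.

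- s = 0: the weights are 0.25 each.
- s = 0.05: the multiplier of t is 0.30 / (0.40 + 0.70) = 0.273. The terms are 1, 0.727, 0.455 and 0.182, with sum 2.364. The weights are 0.423, 0.308, 0.192 and 0.077.

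**4. If T1 to T4 are the responses.**

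| True difference at T1, T2, T3, T4 | s = 0 | s = 0.05 |
|---|---|---|
| 0, 0.35, 0.35, 0.35 | 0.35 × 0.75 = 0.262 | 0.35 × 0.577 = 0.202 |
| 0, 0.35, 0.20, 0.10 (fading) | 0.25 × 0.65 = 0.16 | 0.15 |
| 0, 0.10, 0.20, 0.35 (rising) | 0.25 × 0.65 = 0.16 | 0.10 |

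For the constant effect the loss is 25% to 42%. The standard error at 130 per arm is √(2 × 0.700 / 130) = 0.104 for s = 0 and √(2 × 0.769 / 130) = 0.109 for s = 0.05. Power is Φ(0.262/0.104 − 1.96), about 72%, and Φ(0.202/0.109 − 1.96), about 46%. A chance T1 difference of 0.2 SD contributes directly 0.2 × 0.25 = 0.05 to 0.2 × 0.42 = 0.08, apart from whatever part of it persists at later visits.

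**5. If only T2 to T4 are the responses.** The weights sum to one, so a constant 0.35 is estimated as 0.35, without dilution. With s = 0 the weights are one third each. The fading pattern gives (0.35 + 0.20 + 0.10) / 3 = 0.22, and the rising pattern gives (0.10 + 0.20 + 0.35) / 3 = 0.22. With slope variance the two values move apart, but there is still only one coefficient.

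**6. With group-by-time and T1 adjustment.** The T2 contrast estimates the T2 effect itself, so a true 0.35 is estimated as 0.35. With s = 0 the residual variance at T2 given T1 is 1 − 0.6² = 0.64, the standard error is √(2 × 0.64 / 130) = 0.099, and power is about 94%, again without clustering.

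**The case against.** Four points can be made for the plan.

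- **T1 is not named as a response.** The sentence before the model lists T2, T3 and T4 only, and Table 2 gives the same outcome times. This stands. A reader might infer that the effect is certainly diluted and that baseline imbalance is certainly counted as effect. The text does not settle that. A model of change over time without a baseline covariate would usually take T1 as its first response, but that is an inference, and step 5 shows no dilution of a constant effect without it.
- **An article condenses.** The list names no fixed effect of time either, so it may be shorthand, with the interaction left to a fuller plan. That is possible. But the article chose to give the terms, and the missing one carries the treatment question. If it is shorthand, the wording still describes a different analysis, and an interaction added later would look post hoc. The missing fixed time effect does not change the arithmetic (step 2).
- **Visit-wise analyses are not excluded.** The sentence announcing analysis at T2, T3 and T4 may mean separate comparisons. It names no method for them, and the efficacy question is then assigned to the mixed model. So the claim is that this model cannot separate the visits, not that the trial never could.
- **The variances are assumed.** This stands, and so the size is given as a range. Coding time in months with slope variance 0.05 would lower the rising-effect figure to 0.07, but it implies a T4 variance of 0.6 + 0.4 + 0.05 × 12.75² = 9.13 against 1 at T1. That figure is not relied on.

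**Conclusion.** The point holds, and it does not depend on whether T1 is a response: the model as stated has a single, time-constant treatment parameter and estimates neither the primary outcomes as Table 2 defines them nor the posttest difference behind the 260. That follows from the listed terms alone, and it should be corrected before the analysis.

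The numerical loss is conditional. If T1 is a response, the assumed variances give an estimate of about 0.26 to 0.20 for a true constant 0.35, a T1 weight of 0.25 to 0.42, and power of about 72% to 46% at 130 per arm. If T1 is not a response, a constant effect is recovered in full, and the damage is that differing time courses are merged into one average.

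Two further inferences go beyond the text. One is that the model favours the intervention: under randomisation the expected T1 difference is zero, so averaging it in costs power and clarity and does not inflate the expected effect. The other is that few classes make imbalance likely: the article gives no number of classes. It says only that classes are the randomised units, which in general makes chance imbalance more of a concern than individual randomisation does.

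**What to change.** Replace the model description with one that states:

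- categorical time, group and group-by-time as fixed effects;
- how T1 enters: either T2, T3 and T4 as responses with the T1 score of the same outcome as covariate, or T1 as a response with the arm means constrained equal there;
- a random effect for school class, the randomised unit, which the present list does not contain;
- the adjusted group difference with its confidence interval at each of T2, T3 and T4, with T2 named as the contrast that matches the sample size calculation.

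The cost is analysis wording only. All the scores are already collected at four visits, and no visit, instrument or participant is added. The article reports recruitment as still under way, so the change can be recorded before the analysis.

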### Monitoring study implementation

All the group sessions will be conducted in schools by five registered psychologists, Masters Students. Weekly supervision sessions will be conducted with the therapists in order to solve potential issues that could result in the administration of the intervention. Treatment fidelity and therapists’ adherence to the protocol will be assessed by randomly listening to audio recordings of the sessions.

### Ethics and dissemination

This trial will be conducted in compliance with the Declaration of Helsinki [54]. The study was approved by the Ethics Committee of Babeș-Bolyai University (Registration number: 33215/ 03.06.2016). In Table 2 is presented the trial registration dataset as recommended by World Health Organisation (WHO). Prior to assessment, parents will sign the informed consent, agreeing for their offsprings to participate in the trial. Adolescents will sign the informed assent to participate in the study. Assessment reports contain no personal identifying information. No incentives will be offered for participation. Adolescents will be informed that they can withdraw from the study at any moment.

**Table 2 Tab2:** WHO Trial Registration Data Set

Data category	Information
Primary registry and trial identifying number	ClinicalTrials.gov NCT02756507
Date of registration in primary registry	25 April 2015
Secondary identifying numbers	The Ethics Committee of Babeș-Bolyai University (Registration number: 33215/ 03.06.2016)
Sources of monetary or material support	The Romanian Executive Unit for Financing Education Higher Research, Development and Innovation, Babeș-Bolyai University
Primary sponsor	Babeș-Bolyai University
Contact for public queries	[name] Department of Clinical Psychology and Psychotherapy Babeș-Bolyai University Romania [name] E-mail: [contact]
Contact for scientific queries	[name] Babeș-Bolyai University [name] E-mail: [contact]
Public title	Transdiagnostic REBT Prevention Program for Adolescents
Scientific title	A video-based transdiagnostic REBT universal prevention program for internalizing problems in adolescents
Countries of recruitment	Romania
Health condition(s) or problem(s) studied	Anxiety Depression Internalizing problems
Intervention(s)	Experimental: video-based transdiagnostic REBT prevention program Control: waiting list
Key inclusion and exclusion criteria	Inclusion criteria: Preadolescents and adolescents will have ages between 12 and 17 years old; Are attending middle school or high-school; Adolescents have sufficient understanding of the Romanian language in order to complete assessments at all time points and to participate in the prevention program; Their parents have sufficient understanding of the Romanian language in order to sign the informed consent; Parents will sign the informed consent and adolescents will provide informed assent. Exclusion criteria: Age below 12 or above 17 years; No signed informed consent from parents; Adolescents will score high on suicidal ideation according to (1 item on the Depression subscale from Beck Youth Inventories); Not Romanian-speaking in order to understand the content of the prevention program and to complete the assessments.
Study type	Randomized controlled trial
Date of first enrollment	June 2016
Target sample size	338
Recruitment status	Recruiting
Primary outcome(s)	Anxiety symptoms at T_2_, T_3_, T_4_; the Multidimensional Anxiety Scale for Children Depressive symptoms at T_2_, T_3_, T_4_; the Beck Youth Inventories™ -Second Edition for Children and Adolescents
Key secondary outcome(s)	Maladaptive cognitions at T_2_, T_3_, T_4_; the Children’s Automatic Thoughts Scale – Negative/Positive Comorbid problems at T_2_, T_3_, T_4_; the Strengths and Difficulties Questionnaire Prosocial behaviors Quality of life at T_2_, T_3_, T_4_; the Questionnaire for Measuring Health-Related Quality of Life in Children and Adolescents, The Revised Version – adolescent version Treatment expectancies at T_2_; the Credibility/ Expectancy Questionnaire Satisfaction with the intervention at T_2_; the Client Satisfaction Scale

### Dissemination policy

This trial’s results will be submitted for publication in peer-reviewed journals, focusing on primary and secondary outcomes results, as well as on mechanisms of change. Also, results will be presented at national and international conferences.

## Discussion

Internalizing problems, namely anxiety and depressive disorders are prevalent conditions in adolescents [1], associated with a high burden of disease for families, as well as for the society [3, 4]. Despite the high prevalence and the associated costs of internalizing problems, the problem of treatment accessibility is an important one. In fact, most of these disorders remain undetected and, consequently, untreated, but what is even more, is the fact that even when adolescents receive mental health treatment, only a few receive adequate services [10, 11]. Barriers to the access to adequate mental health care could be tacked if prevention programs would be delivered in school contexts. Universal school delivered prevention programs are great modalities to prevent the onset of youths’ anxiety and depression disorders, two of the most common problems that emerge in adolescence. Therefore, by targeting both anxiety and depressive disorders in a school context, adolescents could learn about their symptoms and benefit on such programs. Also, another considerable barrier to accessing mental health services, namely stigma, would be reduced, as all the adolescents will receive the same program, and their mental health literacy will be improved. Furthermore, youths’ predilection for using technology should be taken into consideration when designing such programs, in order to improve their adherence. Existent advances in information and communication technologies can help to overcome the barriers to the access to mental health services. The aim of the present study is to investigate the efficacy of a video-based transdiagnostic REBT universal prevention program delivered in a school setting as compared with a waiting list control. Furthermore, a second aim of the present study is to investigate adolescents’ irrational beliefs as mediators, namely subsequent mechanisms of change of the prevention program.

There are several limitations that we should consider. First, as we rely only on self-reported data, potential bias can result in the case of adolescents. Another important limitation could be the lack of a placebo condition. However, as this will be the first trial comparing the efficacy of a transdiagnostic video-delivered REBT prevention program, we aim to compare it with a waitlist condition and intend to extend this study and compare it with an active placebo or a traditional face-to-face program. Another limitation is related to the possible dropout at 12-month follow-up assessment, as it is possible that several adolescents entering high school will change their schools or live in a different city.

In conclusion, this is the first study that aims to investigate the efficacy of a video-based transdiagnostic REBT universal prevention program in reducing internalizing problems in adolescents. Also, it is the first study that integrated REBT with technology in the format of a video-based program aimed to reduce anxiety and depression outcomes in youths. Video-based interventions take into consideration young peoples’ predilection to use technology.

Moreover, as indicated in a recent review study analyzing school mental health programs delivered for more than 27 million of children [55], most of the research on the efficacy of prevention programs for children delivered in school contexts was conducted in high-income countries. We, therefore, need to conduct such a study in a Romanian population of adolescents, given the limited existent research on the efficacy of such programs in emerging countries.

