A main limitation of the existent universal prevention programs is the fact that there are no cross-over effects, specifically only those outcomes that are targeted (e.g., anxiety symptoms in universal prevention programs for anxiety) improve, with no significant changes in the non-targeted condition [16]. These findings call for more research into universal prevention programs that are based on transdiagnostic approaches, targeting both anxiety and depression within the same protocol. Research on transdiagnostic prevention programs delivered in school settings is scarce, with only a few studies being conducted [17–20] that show mixed results regarding the efficacy of transdiagnostic universal prevention programs on anxiety and depression outcomes at posttest, short- and long-term follow-up. However, given the high heterogeneity between these studies (e.g., treatment protocol, design, number of sessions) more research needs to be conducted in order to establish the efficacy of transdiagnostic universal prevention programs, as well as on the investigation of the mechanisms of change involved.

Rational emotive behavior therapy (REBT) [21, 22], a form of cognitive behavioral therapy (CBT), which emphasizes the role of irrational beliefs in generating dysfunctional emotions and maladaptive behaviors, has been previously tested as a prevention program for depressive adolescents [23], or as a brief intervention for adolescents with subclinical internalizing problems [24]. REBT is particularly suitable for a transdiagnostic universal prevention program, given the fact that according to its theory, irrational beliefs (e.g., demandingness, catastrophizing/awfulizing, low frustration tolerance and global evaluation of human worth) are transdiagnostic factors involved in emotional problems [25]. Furthermore, evidence coming from a meta-analysis shows that irrational beliefs are significantly associated with distress [26]. Furthermore, the suitability of REBT for transdiagnostic prevention and interventions programs is also indicated by those studies that show that several specific types of irrational beliefs are involved in multiple disorders (e.g., catastrophizing [27] or frustration intolerance [28]). REBT can be easily adapted for different modalities of delivering interventions, such as technologically enhanced interventions. No study, however, investigated the efficacy of an REBT prevention program delivered via technology enhancements.

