
### Aim

The present study aims to investigate the efficacy of a video-based transdiagnostic REBT universal prevention program for internalizing problems in Romanian adolescents, implemented in a school setting. Our second aim is to investigate subsequent mechanisms of change, namely, we want to investigate whether maladaptive cognitions are significant mediators of the prevention program’s efficacy.

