#### Maladaptive cognitions

The Children’s Automatic Thoughts Scale – Negative/Positive (CATS-N/P) [48] will be used to assess negative and positive automatic thoughts in adolescents. CATS-N/P consists of 50 items, rated on a 5 point Likert scale, where 0 means *Not at all* and 4 means *All the time*. Total negative automatic thoughts score is computed by summing the three subscales, namely: Physical Threat, Social Threat, and Personal Failure, consisting of 40 items, while total positive automatic thoughts scale consists of 10 items. This instrument showed adequate psychometric properties (e.g., internal consistency, discriminant validity) previously [48].

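### Mediation is fixed as a single-level PROCESS analysis although classes are randomized, and two passages name a mediator (irrational beliefs) for which no instrument is listed

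*Protocol article*

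**What the plan says.** **Allocation.** The title and the Design section of the protocol article describe a cluster trial in which school classes are randomized to the programme or to the wait list.

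**Mediation method.** The Statistical methods section gives one sentence: "Mediation and moderation analyses will be conducted using PROCESS macro". It names no class term, cluster-robust variance or cluster resampling. The efficacy model in the same section has a random intercept and a random slope for time and a fixed group effect, and names no class or school effect.

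**Mediator.** The Aim section asks "whether maladaptive cognitions are significant mediators of the prevention program", and the Abstract uses the same term. The outcome section headed Maladaptive cognitions assigns this construct to the CATS-N/P, which "will be used to assess negative and positive automatic thoughts in adolescents". Table 2 agrees: "Maladaptive cognitions at T_2_, T_3_, T_4_; the Children’s Automatic Thoughts Scale – Negative/Positive". Two places depart from this. The Discussion states the second aim as "irrational beliefs as mediators, namely subsequent mechanisms of change of the prevention program", and the Statistical methods section lists among the baseline comparisons "anxiety, depressive symptoms, irrationality, comorbid conditions, and quality of life".

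**The concern.** The second aim is the test of the programme's theory. Two separate things weaken it.

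The first is precision. Every pupil in a class has the same allocation, so the treatment-to-mediator effect is estimated from differences between classes. A single-level regression takes its standard error from the spread between pupils and ignores any similarity within classes. If classes differ at all in automatic thoughts, that standard error is too small, and the error carries into the indirect effect.

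The second is the construct. The Background defines irrational beliefs as "demandingness, catastrophizing/awfulizing, low frustration tolerance and global evaluation of human worth", gives them as the reason REBT suits a transdiagnostic programme, and sessions 3 and 4 work on them. If a mediated effect on automatic thoughts were read through the Discussion's wording, it would appear to confirm a mechanism for which the article lists no measure.

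**Working it through.** **1. The plan's own figure.** The article gives no figure for mediation. Its only power calculation is 260 pupils for d = 0.35, two-sided alpha 0.05 and power 80% (Sample size calculation). The normal approximation gives 2 × (1.960 + 0.842)² / 0.35² = 128.2, so 129 per arm and 258 in total. The exact noncentral t calculation gives 130 per arm and 260 in total, with power 0.803. The stated figure is reproduced for independent pupils, so it contains no allowance for clustering.

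**2. Treatment-to-mediator path.** Neither class size m nor ICC is in the article, so both are assumed, with m from 15 to 25 and ICC from 0.01 to 0.05.

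- Design effect: DE = 1 + (m − 1) × ICC
- Factor by which the naive standard error is too small: √DE
- True size of a nominal 5% test: 2 × (1 − Φ(1.96 / √DE))

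| m | ICC | DE | √DE | True size |
|---|---|---|---|---|
| 15 | 0.01 | 1.14 | 1.07 | 6.6% |
| 15 | 0.02 | 1.28 | 1.13 | 8.3% |
| 15 | 0.05 | 1.70 | 1.30 | 13.3% |
| 25 | 0.01 | 1.24 | 1.11 | 7.8% |
| 25 | 0.02 | 1.48 | 1.22 | 10.7% |
| 25 | 0.05 | 2.20 | 1.48 | 18.6% |

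**3. Indirect effect.** The formula covers one path only, so the indirect effect was checked by simulation. The first set-up had 16 classes of 21, no treatment effect on the mediator, a mediator-outcome coefficient of 0.5, and 1,000 runs. A single-level percentile bootstrap of the indirect effect rejected the true null in 5.5% of runs at ICC 0, 7.0% at 0.01, 10.6% at 0.02 and 18.8% at 0.05.

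A second set-up, with 14 classes of 24 and 400 runs, gave 12% at ICC 0.02 and 21% at 0.05 with the same coefficient. It gave under 1% when the mediator-outcome coefficient was zero. The inflation of the indirect-effect test therefore depends on a non-zero mediator-outcome path.

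**4. Would resampling classes be enough?** With 25 per class, 338 / 25 = 13.5, so about 14 classes. In the second set-up, a class-level percentile bootstrap rejected the true null in 8% of runs at ICC 0, 10% at 0.02 and 10.5% at 0.05. The Monte Carlo error at 10% is √(0.10 × 0.90 / 400) = 1.5 percentage points. At ICC 0.02 this cannot be told apart from the single-level method, and at 0.05 it is still about twice nominal.

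**5. The mediator, place by place.**

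| Place | Term | Instrument listed |
|---|---|---|
| Abstract; Aim | maladaptive cognitions | CATS-N/P |
| Maladaptive cognitions; Table 2 | maladaptive cognitions, scored as automatic thoughts | CATS-N/P |
| Statistical methods, baseline comparisons | irrationality | none |
| Discussion | irrational beliefs | none |

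The CATS-N/P negative score is built from "Physical Threat, Social Threat, and Personal Failure, consisting of 40 items"; the other 10 items score positive thoughts. These scale names are not the four beliefs in the Background's definition.

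**The case against.** **The aim is measured.** A reader might infer from the Discussion that the second aim has no instrument and cannot be tested. The documents do not support that. The Abstract, the Aim, the outcome section and Table 2 consistently tie maladaptive cognitions to the CATS-N/P. The mismatch is confined to one Discussion sentence and one word in a baseline list. This objection stands, and it limits the naming point to a correction of wording and of the conclusion.

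**Misreporting is not planned.** Nothing in the article says that change in automatic thoughts will be published as change in irrational beliefs; the wording only leaves room for it. Nor do the documents show the CATS-N/P items, so one cannot say that no item touches such a belief, only that no listed scale is described as scoring them. Fig. 2, the instrument overview, is not shown, although the outcome text and Table 2 make a further scale unlikely.

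**The size is assumed.** This also stands. With parental consent required, 25 participants per class may be high, and at 15 per class and ICC 0.01 the true size is only 6.6%.

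**Clustering could be left to an analysis plan.** This does not stand. The article fixes the tool, and the named tool is single-level. Adding class indicators as covariates would not rescue it, because allocation is constant within a class. The Randomization and blinding section does speak of randomization within classes, but it also requires equal numbers of experimental and control groups in each school, and the title and Design section say cluster.

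**Overlap.** The missing class term also affects the efficacy model. It is one underlying defect and should not be counted twice.

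**Conclusion.** The point holds in two parts of unequal weight.

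The main part is the method. As written, the mediation analysis gives intervals and tests that are too narrow for the treatment-to-mediator path, and for the indirect effect when the mediator-outcome path is non-zero. Under the assumed 15 to 25 pupils per class and ICC of 0.01 to 0.05, the nominal 5% test of the treatment-to-mediator path runs at about 7% to 19%. The direction follows from class allocation and any positive ICC; the size rests on those assumptions.

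The lesser part is the label. A conclusion about automatic thoughts remains available once class is handled. A conclusion about irrational beliefs is not supported by any instrument listed in the text or in Table 2. Because the aim is secondary, this is something that should be corrected; it does not undermine the trial.

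**What to change.** 1. In Statistical methods, replace single-level PROCESS with a two-level mediation model with class random effects and a small-sample correction for the number of classes. Do not rely on an uncorrected class-level percentile bootstrap with roughly 14 to 16 classes. Use the CATS-N/P at T2 as mediator and anxiety and depression at T3 and T4 as outcomes.
2. Name the mediator as CATS-N/P automatic thoughts in the Discussion and in the baseline comparisons, in line with the Aim and the outcome section, and limit the mechanism conclusion to that construct. A sponsor who wants to keep the claim about irrational beliefs would have to add a measure of them.

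**Cost.** Items 1 and 2 need no new data, since all these assessments are already planned. The work is a different analysis routine and some rewording. The intervals for the indirect effect become wider, and the claim about mechanism becomes narrower.
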